#### Reaction Time

To analyse the reaction time, the software TRT_S2012 will be used [constructed and validated by (71)]. The software proposes a simple total reaction time (TRT) test, which consists of the appearance of a yellow square (parameterisable) in the centre of the monitor at predefined time intervals (ranging from 1.5 to 6.5 ms) and, when it is presented, the participant should react as quickly as possible by pressing the spacebar of the computer keyboard (Figure 4).

**Figure 4 F4:**
[figure not shown]
Reaction time task.

## Assessment Protocol

The assessment protocol will have the following sequence: the assessment scales will be undertaken with the participants' parents in a separate room (PEDI, Abilhand-Kids, and *ACTIVLIM-CP*), and GMFCS and MACS will be carried out by observacional analysis of their abilities. Also, cognitive (WISC-IV) and visual assessments (*Titmus Test and Ishihara Test)* will be made by a psychologist and a psychometrist, respectively.

Then, for the VR assessment, the coincident timing task will be carried out with a short-term motor learning protocol as used by Monteiro et al. (17), with 20 repetitions for acquisition. After 15 min of no contact with the task, the participants will perform five repetitions of the same task (for retention analysis), and five more repetitions with a speed increase (for transfer of performance analysis).

The reaction time task will be carried out with two attempts of adaptation and 10 attempts for analysis, as used by Crocetta et al. (71).

The HRV will be assessed by 20 min of rest seated in a comfortable chair or their own wheelchair, as used by Alvarez et al. (72).

The assessment part of the protocol will take around 1 h and 30 min in total (inferential analysis method follows in the item “Data analysis”).

## Intervention

All participants will attend the assigned tDCS and VR intervention as follows: there will be 20 sessions over 4 weeks with tDCS and non-immersive VR tasks, 10 of which will involve active tDCS combined with VR tasks and 10 will involve sham tDCS combined with VR tasks, separated by a 1 month washout period. The sessions will be administered consecutively and once a day (except for weekends). The investigators will have certification to apply the tDCS in children and adolescents with CP and will have experience of the VR tasks.

### VR Intervention

During application of the active or sham tDCS, in all sessions the participants will perform tasks in a non-immersive VR environment to stimulate and verify improvement of motor performance. Thus, we will use the *Bridge Games* software tasks [for details and publication, see (68, 71)]. The software that will be used was developed by the Research Group and Technological Applications in Rehabilitation (Grupo de Pesquisa e Aplicação Tecnológica em Reabilitação–PATER) group from the School of Arts, Sciences, and Humanities of the University of São Paulo (EACH-USP) (12).

The two tasks that will be used are presented below.

#### MoveHero

*MoveHero*, as presented by Martins et al. (68), is a game that displays falling spheres in four imaginary columns on the computer screen, with a musical rhythm selected by the researcher. This is also considered a coincident timing task; the action is to react (using the upper limbs) and not let the balls pass from the fixed targets. The spheres should only be intercepted when they reach the targets allocated in parallel (at two height levels), two on the left (left position targets A and B) and two on the right of the participant (right position targets C and D), as shown in Figure 5. The virtual contact is performed by the avatar of the individual, i.e., a representation of the individual appears on the computer screen. The individual moves their arms and trunk (only if they can move the trunk) in front of the webcam to coincide with the moment the ball touches the target. The individual is positioned at a distance of 1.5 m metres from the computer monitor and waits for the balls (which fall randomly on each target) to drop. The avatar's hand should reach the target sphere along with the arrival of the ball, and the game offers feedback on correctness and error by means of changing the spheres' colour (green for correct and a red line for error).

**Figure 5 F5:**
[figure not shown]
Representative design of the *MoveHero* software performed during tDCS intervention. **(A)** Demonstration of hit performed by the participant (green light). **(B)** Error performed by the participant (red bar).

#### Moviletrando

The computer game *MoviLetrando* was developed at the Laboratory for Research on Visual Applications in the State University of Santa Catarina, Brazil (73, 74). It has been used in different studies [see (75, 76)]. The game uses the concept of projection-based VR with a webcam and creates a mirror images so that participants can see themselves on the screen (Figure 6).

**Figure 6 F6:**
[figure not shown]
Representative design of the *Moviletrando* software performed during tDCS intervention.

As presented by Guarnieri et al. (75), *MoviLetrando* is a face-to-face learning computer program that involves interaction with virtual symbols projected on the screen: letters of the alphabet (vowels and/or consonants) and numbers (1 to 10). The software allows the therapist or education professional to control different phases that are identifiable as alphabet phases (AP) and numbers phases (NP). In each phase, the software offers various levels of difficulty (generating symbols on the left side, on the right side, or both sides; an increase/decrease in the number of symbols; an increase/decrease the size of the symbols; and an increase/decrease in the time of the exposure to symbols). For this study we chose two phases (one alphabet and one number). The game shows a symbol (an alphabet or number according to the phase) in the top middle of the screen, and the participant has to reach the same symbol, moving his/her hands in the virtual environment. The score obtained is based on whether or not participants reach a symbol, whether it is correct, and the elapsed time taken to carry out each task.

### tDCS Intervention

#### Active tDCS

The anodal active tDCS will be performed over 10 consecutive sessions per weekday (i.e., one session daily, no stimulation during the weekend) during the practice of VR games. The active tDCS will be performed with a current of 1 mA and 20 min of duration (and 30 s of ramp-up and ramp-down). The stimulation target will be the M1 area and aimed at the elbow, shoulder, and trunk of the Penfield homunculus (i.e., 10% instead of 20% laterally to CZ), choosing the more functional side of the participant (C1 or C2 areas of the International 10–20 System for EEG).

#### Sham tDCS

The sham tDCS will be performed over 10 consecutive sessions per weekday (i.e., one session daily, no stimulation during the weekend). However, the electrodes will be positioned at the same sites of the active tDCS and the device will be switched on for 30 s (ramp-up), giving the children the initial sensation of the 1 mA current, but with no stimulation administered the rest of the time (32). The current will be interrupted after 30 seconds. This sham protocol is already programmed in the device prior to data collection.

## Procedure

During the tDCS combined with VR protocol, participants will be seated comfortably in an ordinary chair or their own wheelchair, with their hands arranged over their legs and their feet resting on the floor (or on the wheelchair support). The demarcation and application of the active TDCS will then be performed in the cortical area corresponding to the C1 and C2 primary motor cortex according to the International 10–20 System for EEG (area M1), in order to reach the elbow, shoulders, and trunk.

Therefore, anodal tDCS with electrodes with 25 cm^2^, intensity of 1 mA and a density of up to 0.057 mA/cm^2^ for a period of 20 min will be used. The same active procedure setting will be used for the sham (placebo) procedure; however, the current will be interrupted after 30 s (32). This configuration will ensure that the electrical stimulus is interrupted before generating considerable stimuli, while the other characteristics of the intervention will be maintained. After each session the participants will be questioned about the presence of any adverse effects. The device used will be the DS-Stimulator Mobile from NeuroConn, which allows blindness of the subjects of the research and the experimenters.

After 5 min of stimulation, the individuals will perform the VR training. The protocol will count on the execution of the following sequence of games: *MoveHero* for 5 min and *Moviletrando* for another 5 min. The participants will have the rest of the time (5 min) with tDCS (sham or active) only. The training time will take 20 min in total. This kind of protocol was used by previous authors who used tDCS (22). The method of inferential analysis follows is described in the “Analysis of the data” section of this paper.

## Primary Outcome

To evaluate the effect of the combined therapy of virtual reality and tDCS in the upper-limb and trunk motor area on M1 (C1 or C2) of individuals with CP, and to check the possibility of generating motor gains in individuals with CP, we will observe the change from baseline motor values provided by different scales and VR tasks.

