Study type interventional allocation	Randomised
Masking	Triple-blinded
Assignment	Crossover
Primary purpose	Treatment
Date of first enrolment	March 2019
Target sample size	35
Recruitment status	Recruiting
Primary outcome(s)	Motor skills improvement
Key secondary outcome(s)	HRV improvement

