**Figure 2 F2:**
[figure not shown]
Study design. MACS, Manual Ability Classification System; GMFCS, Gross Motor Function Classification System; PEDI, Pediatric Evaluation of Disability Inventory; VR, virtual reality; n: sample size; tDCS, transcranial direct current stimulation; D0-D11, days of interventions in which D0 is the baseline, D1 to D10 are the days of interventions and the D11 is the day of the final assessments. Participants and sampling.

Thirty-six participants will be recruited through referral by the coordinators of three clinics in Brazil: *Intensiva, Intertherapy*, and *Therapies*, located in São Paulo state. Those interested in participating will undergo a detailed screening using the eligibility criteria for enrolment in the study.

The sample size was calculated using statistical software (GPower 3.1.5) on the main outcome measure (i.e., the motor score). This calculation was based on data from one study with a group of individuals with CP who received tDCS (32). The power was 0.80; the alpha was 0.05; and the effect size was 0.65 (Cohen's d). The sample estimation indicated that 28 participants would be necessary (i.e., 14 per group). With an adjustment to allow for a withdrawal rate (20%), we will recruit 36 participants.

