### Assessments to Characterise Participants and Measure Improvement

#### Pediatric Evaluation of Disability Inventory (PEDI)

The PEDI is a standardised instrument consisting of a structured interview with the caregiver, capable of documenting the functional performance of children between 6 months and 7 years old in their daily life activities (39, 40).

This test covers three domains: self-care, mobility, and social function. The self-care scale covers food, personal hygiene, toilet use, clothing, and toilet control. The functional items of mobility provide information about transfers, walking indoors and outdoors, and use of stairs. The social function dimension reflects issues related to communication, problem solving, interaction with colleagues, amongst others.

Total scores are calculated for each scale in each domain, where each item receives a score of 0 (the child is unable to perform the activity) or 1 (the activity is part of the child's repertoire), and the sum of the items generates the score for each domain. Studies have shown that the PEDI test is valid and sufficiently reliable to be applied to children with CP in Brazil (40, 41).

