### Assessments for Primary Outcome

The VR task will be used to assess the participants' motor abilities (accuracy, precision, and trend of anticipation or delay in movement) during each intervention. Also, we will use coincident timing and reaction time tasks, ABILHAND-Kids, ACTIVLIM-CP, and visual and cognitive assessments to characterise the group and to find influences on motor improvement by using correlation tests. These tests will be carried out at three stages: initial assessment (D0); assessment after five interventions (D5) and final assessment (D11) (Figure 1).

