## Statistical Analysis

For the coincident timing task for the inferential analysis of the initial tasks (transversal) and the longitudinal protocol with tDCS and HRV as dependent variables, the error measures (constant, absolute, and variable errors) will be considered (time in milliseconds). If the data meet the assumptions for the use of parametric analysis, ANOVA will be performed to identify intra and inter-group differences. These, if any, will be detected by the *post hoc* Tukey-HSD test. If the normality assumptions are not met, non-parametric analyses will be undertaken to identify and locate the differences: a Friedman and *post hoc* Wilcoxon test (for within groups) and a Kruskal–Wallis and *post hoc* Mann–Whitney *U*-test (between groups). For the between-groups analysis of HRV indices, MANOVA will be used, with repeated measures for within groups analyses (for evaluations and follow-up) or Mann–Whitney for intergroup analyses and Friedman for intragroup analyses. A significance level of 0.05 (5%) will be defined; all intervals constructed throughout the work will be 95% statistical confidence. The statistical program used will be SPSS (Statistical Package for Social Sciences), version 26.0.

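### No single primary motor measure or time point is fixed, the sample-size motor score matches no listed instrument, and no control across outcomes is stated, so the chance of a false-positive motor result exceeds 5%

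*Protocol article*

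**What the plan says.** The Primary Outcome section says that "we will observe the change from baseline motor values provided by different scales and VR tasks". The registration table (Table 1) gives the primary outcome only as "Motor skills improvement".

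The section Assessments for Primary Outcome starts with the VR task, used during each intervention for accuracy, precision and direction of timing error. It then says "we will use coincident timing and reaction time tasks, ABILHAND-Kids, ACTIVLIM-CP, and visual and cognitive assessments to characterise the group". A second purpose given for these instruments is "to find influences on motor improvement by using correlation tests". The visits are "initial assessment (D0); assessment after five interventions (D5) and final assessment (D11". The Introduction also expects retention at 30 days, and the Discussion at 15 and 30 days; neither appears in that visit list.

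The sample size, given in the participants and sampling text after Figure 2, was calculated "on the main outcome measure (i.e., the motor score", with power 0.80, alpha 0.05 and Cohen's d 0.65. The result is 28 participants, raised to 36 for withdrawals.

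In the Statistical Analysis section, for coincident timing, "the error measures (constant, absolute, and variable errors) will be considered (time in milliseconds". ANOVA with post hoc Tukey-HSD is planned if parametric assumptions hold. Otherwise Friedman with Wilcoxon and Kruskal–Wallis with Mann–Whitney are planned. One significance level of 0.05 is set.

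**The concern.** A primary outcome has to identify the result on which the trial will be judged. Here the reader cannot tell which instrument, which metric or which visit that is. If active tDCS beats sham on one motor measure and not on the others, the text lets that measure be presented as the primary finding. The 5% error rate then no longer applies to the claim that motor function improved.

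The power statement has the same gap. It belongs to a motor score, and nothing in the assessment sections carries that name, so the 80% cannot be attached to any analysis the article describes.

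**Working it through.** **1. The plan's own figure.** Inputs from the sample-size text: d = 0.65, alpha 0.05, power 0.80, stated n = 28 (14 per group). The test and its sidedness are not given. Exact noncentral-t calculations give:

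- paired t-test: 21 in total two-sided, 17 one-sided;
- two-sample t-test: 39 per arm (78 in total) two-sided, 30 per arm (60) one-sided.

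None gives 28. A repeated-measures ANOVA can reach 28, but only with unstated inputs, for example f = 0.325, four measurements and correlation 0. The calculation therefore does not reveal which measure or analysis was sized.

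**2. Where the motor measures are mentioned.**

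- Primary Outcome: change from baseline on scales and VR tasks, none singled out.
- Assessments for Primary Outcome: five motor instruments at three visits. The sentence naming the timing and reaction-time tasks and the scales ties them to characterisation and correlation.
- Introduction (hypothesis): benefit on functional scales, reaction time and coincident timing, larger with active tDCS.
- VR Task for Assessment: both computer tasks are to assess improvement with the intervention.
- Statistical Analysis: only the three coincident-timing errors and HRV (the secondary outcome) are named for inference.

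The number of efficacy tests can thus be read in more than one way. Three reference counts cover the main readings:

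- 3: constant, absolute and variable timing error;
- 6: those three plus reaction time, ABILHAND-Kids and ACTIVLIM-CP, at one visit;
- 12: the same six at D5 and at D11, tested separately.

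**3. Chance of at least one false positive.** Assume no true effect on any measure and each test at two-sided 0.05. For k independent tests the chance is 1 − 0.95^k:

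- k = 3: 1 − 0.857 = 0.143
- k = 6: 1 − 0.735 = 0.265
- k = 12: 1 − 0.540 = 0.460

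For correlated tests, equally correlated normal test statistics were simulated (400,000 draws), counting draws in which any |Z| exceeded 1.96.

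| Tests | Correlation 0 | 0.5 | 0.7 | 0.9 |
|---|---|---|---|---|
| 3 | 14.3% | 12.5% | 10.9% | 8.4% |
| 6 | 26.5% | 20.8% | 16.4% | 10.9% |
| 12 | 46.0% | 32.0% | 23.3% | 13.5% |

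Twelve is not a ceiling. The Assessment Protocol splits coincident timing into acquisition, retention and transfer blocks. Three errors in three blocks make nine tests from one task at one visit: 1 − 0.95^9 = 0.37 if independent.

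**4. The price of keeping several co-primaries.** Assume a paired two-sided t-test with d = 0.65 on every measure, and Bonferroni. Six tests at 0.05/6 = 0.0083 need 33 completers, and 28 completers give power 0.72 for each test. Twelve at 0.05/12 = 0.0042 need 37, and 28 give 0.62. A single test at 0.05 with 28 completers has power 0.91.

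**The case against.** The strongest reply is that the article does not plan a 0.05 test of every item. Its inference section names only the three timing errors and HRV. Reaction time and the two questionnaires are described as descriptors and correlates. Visits can be levels of one ANOVA, with Tukey-HSD covering the comparisons between them. On that reading there are three closely related tests, and the error rate is about 8% to 14%.

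This stands as a limit on the size. A reader might infer that each measure is tested separately at 0.05 and that the false-positive chance is therefore 20% to 45%. The article does not support that as a statement of fact: the count and the correlation are both assumptions, and several plausible combinations fall below 20%.

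It does not remove the point. The Primary Outcome section and the hypothesis treat the scales as evidence of improvement, so which measures are efficacy tests remains unsettled. Tukey-HSD acts within one ANOVA and not across outcomes, and the non-parametric route states no adjustment. An analysis plan that is not shown may hold multiplicity details, and their absence alone would be no finding. The choice of primary outcome is different: the article has a section for it, and that section leaves it open.

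Two further inferences should be resisted. A reader might object that constant error is signed, so that anticipators and delayers cancel. The article lists direction of error separately from accuracy and precision, and nowhere calls a lower mean constant error an improvement. A reader might also add PEDI, which is described as "capable of documenting the functional performance of children between 6 months and 7 years old in their daily life activities" while enrolment runs to 14. That mismatch is real, but PEDI is not in the primary assessment list and does not feed this error rate, so it is a separate point.

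**Conclusion.** The point holds in this form: no primary measure, time point or order is fixed; the motor score behind the sample size is not identified; and no control across outcomes is stated. Every combination examined puts the false-positive chance for the motor claim above 5%, from about 8% (three timing errors, correlation 0.9) to 46% (twelve independent tests), with 21% to 26% for six measures at correlation 0.5 to 0. These figures assume that no measure has a true effect and that any one significant result would be claimed. The existence of the problem follows from the text; its exact size does not.

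**What to change.** Before unblinding, name one primary measure and one time point. One workable example is coincident-timing absolute error, change from D0 to D11 of the same period, active versus sham. The sponsor may choose another listed measure; what matters is that the choice is single and made blind. The Blinding section keeps the statistician blind until after the analysis, so this can be done without bias as long as that still holds.

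State which measure the motor score is, and redo or restate the sample size for the named endpoint, with the test, the sidedness and the meaning of d = 0.65. Make the other motor measures and D5 secondary or exploratory, and say which are efficacy tests and which are only descriptors or correlates. Bring the Primary Outcome section, Table 1 and the registry entry into line.

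The cost is wording and a registry update, and the other measures lose primary status. With one named primary no adjustment across the motor measures is needed for the primary claim. If several co-primaries are kept, the sponsor should state the adjustment and accept the loss of power or the larger sample shown in the working.

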### Assessments for Primary Outcome

The VR task will be used to assess the participants' motor abilities (accuracy, precision, and trend of anticipation or delay in movement) during each intervention. Also, we will use coincident timing and reaction time tasks, ABILHAND-Kids, ACTIVLIM-CP, and visual and cognitive assessments to characterise the group and to find influences on motor improvement by using correlation tests. These tests will be carried out at three stages: initial assessment (D0); assessment after five interventions (D5) and final assessment (D11) (Figure 1).

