The benefits of tDCS include the flexibility to use it for different activities and exercises (as it presents a mobile characteristic) and the possibility of combining it with other interventions. Spampinato et al. (25) showed that the combination of tDCS with a task using reward characteristics produced neurophysiological modulation of inhibitory networks, and it resulted in enhanced retention of the learned task. Thus, it can be used during fine motor tasks [to reinforce learning of coordinative tasks; (26)], global movements [to increase range of movement; (22)] and physical activities [in order to facilitate motor activities; (12)], and to improve heart and autonomic conditions (27).

Some studies have produced positive results when combining VR and tDCS therapies in stimulating the lower limbs for gait improvement (12) and balance (28, 29). However, no studies have investigated VR and tDCS interventions using an upper limb motor task, which might benefit different clinical conditions of individuals with CP. We organised a triple-blinded, randomised, and controlled crossover trial to investigate the upper limb motor function of individuals with CP with the aims of (1) investigating the effectiveness of the use of tDCS while performing a non-immersive VR task on upper limb motor function and (2) to analysing the influence of a combined VR and tDCS in upper limb motor function through different functional assessment scales, reaction times, and coincident timing analysis, as well as physiological analyses such as heart rate variability.

We hypothesise that all individuals with CP will show an improvement in performance after practising a non-immersive virtual reality task, with benefits in upper limb functional scales, reaction times and, coincident timing analysis underpinned by an adaptation of autonomic neural physiological control after the protocol, and retention of these variables at the 30-day follow-up. However, such improvement and benefits will be more evident after the application of active tDCS than the sham (placebo) tDCS group. If this hypothesis is confirmed, the results of this study will be relevant to the treatment of individuals with CP.

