### VR Task for Assessment

We will use two VR tasks to assess the participants' capacity and improvement with intervention. The tasks will be used as assessment at three points: initial assessment (D0); assessment after 5 sessions (D5); and final assessment (D11).

The assessment tasks are presented below:

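### The planned correlation tests allow a motor score to be correlated with its own change from baseline, where a negative correlation is expected even if nothing influences improvement

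*Protocol article*

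**What the plan says.** Under Primary Outcome, motor gain is defined as a change score: "we will observe the change from baseline motor values provided by different scales and VR tasks". Assessments for Primary Outcome then names the tools: "we will use coincident timing and reaction time tasks, ABILHAND-Kids, ACTIVLIM-CP, and visual and cognitive assessments". Besides describing the group, their purpose is given as "to find influences on motor improvement by using correlation tests". They are scheduled at D0, D5 and D11.

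The same measures also supply the improvement. VR Task for Assessment says of coincident timing and reaction time: "We will use two VR tasks to assess the participants' capacity and improvement with intervention". ABILHAND-Kids and ACTIVLIM-CP stand under a heading that gives them both roles, describing participants and measuring improvement.

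The Introduction expects that "all individuals with CP will show an improvement in performance after practising a non-immersive virtual reality task", and expects the gain to be larger after active than after sham tDCS. The Statistical Analysis section does not mention the correlation tests.

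**The concern.** A change score contains the baseline with a minus sign. Measurement error that makes a child look poor at D0 also makes that child appear to improve by D11. A plain correlation of D0 with D11 minus D0 therefore tends to be negative even when true status has nothing to do with true change. For timing errors and reaction times, where high is bad, this appears as worse children improving more. For the functional scales, where low is bad, the message is the same.

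If the clause is followed in this way, the report could name baseline motor ability as an influence on improvement when the result is largely arithmetic. A second limit concerns interpretation. Improvement within a treatment period combines VR learning with any tDCS effect, so even a sound correlation with it describes who improves, not who improves because of active stimulation.

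**Working it through.** The article states no figure for the correlation analysis, so there is none to reproduce.

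**Inputs from the protocol article**
- Evaluable n = 28 and recruited n = 36 (sample-size paragraph).
- Significance level 0.05 (Statistical Analysis), taken here as two-sided.
- Improvement = change from baseline (Primary Outcome).

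**Assumed inputs**
- r, the correlation between D0 and D11 of the same measure, from 0.5 to 0.95. The article gives no reliability or standard deviation.
- Equal variance at D0 and D11.
- No link between true status and true change.

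**Expected correlation of a baseline X with its own change Y - X**

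corr(X, Y - X) = (r·sY - sX) / sqrt(sX² + sY² - 2·r·sX·sY)

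With sX = sY this is (r - 1)/sqrt(2(1 - r)) = -sqrt((1 - r)/2). For example, at r = 0.7 it is -sqrt(0.15) = -0.39.

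**How often this reaches p<0.05.** The critical |r| is 0.374 at n = 28 and 0.329 at n = 36. From 20,000 simulated trials per cell:

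| assumed r | expected correlation | n = 28 | n = 36 |
|---|---|---|---|
| 0.5 | -0.50 | 81% | 89% |
| 0.7 | -0.39 | 55% | 67% |
| 0.8 | -0.32 | 38% | 48% |
| 0.9 | -0.22 | 21% | 26% |
| 0.95 | -0.16 | 13% | 15% |

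The nominal rate is 5%.

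**Where the artefact does not arise.** One measure at baseline was correlated with the change in a different measure. The predictor was correlated 0.6 with the true score, and errors were independent. The mean correlation was about zero and the rejection rate was 5.0% at both sample sizes. Visual and cognitive predictors are likewise outside the problem, because their scores are not part of the change.

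**Improvement versus benefit from tDCS.** Take a characteristic that predicts change equally under active and sham (correlation 0.3 or 0.5 with change in each period), with no interaction with tDCS.
- Against improvement averaged over the two periods, it is significant in 60% (0.3) or 96% (0.5) of trials at n = 28, and in 71% or 99% at n = 36.
- Against the within-child active-minus-sham difference, it is significant in about 5%.

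The first result is a correct finding about prognosis. It says nothing about who gains from active stimulation.

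**The case against.** The strongest objection is that the article never pairs a score with its own change. Assessments for Primary Outcome first says the VR task tracks motor abilities during each intervention, and only then lists the other tests as possible influences. The VR Intervention section also says the training games serve to verify improvement. On that reading, improvement comes from the games and the listed tests are separate predictors, which gives no artefact if errors are independent. This stands in part: the coupled pairing is inferred. It is nevertheless a natural reading, because Primary Outcome and VR Task for Assessment take improvement from the scales and assessment tasks themselves, and nothing excludes it.

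Three further objections hold.
- The false-positive rate depends on an unknown r. The article calls ACTIVLIM-CP reliable, and a sample spanning GMFCS I to IV and ages 4 to 14 would tend to raise r, so the lower rows of the table matter.
- A reader might infer that active and sham periods will be pooled. The article does not say how they are combined.
- A reader might infer that the authors mean to identify who benefits from tDCS, or to select children for therapy. The text speaks only of motor improvement and proposes no selection rule. What relates to improvement is a legitimate prognostic question.

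It can also be said that time points, adjustment and the number of tests belong in an analysis plan that is not shown. That is fair for those details. The method itself, simple correlation with improvement, is stated in the article.

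**Conclusion.** The point holds in a conditional form. The article fixes simple correlation tests against motor improvement and lets four motor measures be both predictor and source of the change. Wherever a baseline is correlated with its own change, the result is biased, with a false-positive rate of about 81% down to 13% at n = 28 (89% down to 15% at n = 36) for r from 0.5 to 0.95.

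These figures rest on the assumed r, on equal variances and on no true relation. If scores spread out by D11, the bias shrinks; if they draw together, it grows. They apply only to same-measure pairs.

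The stronger reading, that the trial will report false influences, is not supported, because the pairing is not stated and the rate is far from certainty when r is high. That a correlation with improvement does not show who benefits from tDCS is a limit on interpretation, not an error in the text. The primary active-versus-sham comparison is not touched. This is a minor but free improvement.

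**What to change.** In Assessments for Primary Outcome, replace the simple correlation tests as follows.

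1. **Prognosis.** Regress D11 on D0 of the same measure plus the characteristic of interest. State that no motor score will be correlated with its own change. Read the coefficient as prediction among children with equal measured D0. Because D0 carries error, it is not proof of a causal influence.
2. **Benefit from active tDCS, if that is the question.** Fit a characteristic-by-treatment term in the crossover model, or regress each child's active-minus-sham difference at D11 on the characteristic measured at the first D0, with sequence in the model so that a period effect does not enter. With the D11 difference and a separate first baseline, the simulated false-positive rate was 4.9% at r = 0.5 and 0.7.
3. **Reporting.** Label these analyses exploratory and state how many are run.

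The cost is a change of wording and of analysis code; the data and visits stay the same. Fewer associations will reach significance, and with about 28 children the treatment-interaction analyses will be imprecise, so estimates with confidence intervals are more useful than tests.
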